**Figure 1 F1:**
[figure not shown]
Flow chart of the study based on CONSORT criteria.

### Participants and eligibility and discontinuity criteria

Participants diagnosed with SCD will be enrolled from health units at municipalities of the 31st Regional Health Directorate (DIRES—BA) and in Reference Centers for treatment of SCD in the municipalities of Salvador and Feira de Santana, the two largest cities in the State of Bahia, Northeastern Brazil. SCD is more prevalent in this region of the country. Enrollment of participants will take place between March 2016 and December 2019. The study will be advertised in the SCD reference centers and health care facilities in the two cities. To improve adherence to the intervention protocol, all participants will receive financial aid for round-trip transportation, as well as a meal voucher. In addition, they will receive SCD care recommendations. At the end of the study, all participants will be offered the most effective intervention.

To homogenize the sample, only participants with SCD of HbSS and HbSC genotypes suffering from chronic pain secondary to femoral head osteonecrosis will participate in this study. Theses genotypes were chosen because they are more prevalent, and both have a higher prevalence of femoral head osteonecrosis in adult individuals (Milner et al., 1991). Further eligibility and discontinuity criteria of this study are listed below.

#### Inclusion criteria

Chronic pain secondary to hip osteonecrosis of at least 6 months of duration;Pain intensity above 3 in a 11 points visual analogic scale (VAS);Individuals from both sexes, between 18 and 50 years of age.

#### Exclusion criteria

Any contraindication to use TMS and tDCS such as: cochlear implant, cardiac pacemaker or metal implantation in the skull/brain; drug treatment that modifies the threshold of neuronal activation (i.e., antidepressant, anticonvulsant, and antipsychotic); history of seizure or epilepsy; and pregnancy;Neuropathic pain screened by the *Douleur Neuropathique* 4 questionnaire (DN-4) (Santos et al., 2010);Metal implants at the PES site;Occurrence of infectious disease in the week before inclusion in the study.

#### Discontinuity

Moderate adverse effect (i.e., discomfort enough to interfere with patient's usual activities) or severe (i.e., significant impairment of the patient's usual activities or even total disability, and life threatening) during neurophysiological evaluation or intervention;Participant withdraws consent at any stage of the study.

### Interventions

An experienced physical therapist will manage the intervention protocols. During the intervention, participants will be comfortably seated in a chair, in silence. They will be encouraged to make no cognitive effort, such as mathematical calculations or complex reading. tDCS will be applied with a proper device (tDCS stimulator–TCT, China) connected with two silicon-sponge 5 × 7 (35 cm^2^) electrodes embedded in saline solution (0.9%). The anodic pole will be placed in the motor cortex region (M1) contralateral to the painful hip (or more painful in cases of bilateral symptoms) (locations C1 or C2, according to the 10/20 International EEG System). The cathodic pole will be placed over the contralateral supra-orbital region (locations Fp2 or Fp1, according to the 10/20 International EEG System). The 2 mA stimulation will last 20 min, ramped up and down for 30 s at the initial and final stages of stimulation. A clinical pulse generator (Endophasys, KLD Medical Products, Brazil) will be used to administer PES using 35 cm2 dischargeable electrodes located on the side of the most painful hip. The stimulation will start together with tDCS and will be held for 30 min. The intensity will be maintained at the sensory level, characterized as a comfortable intensity just under motor threshold, with pulse rate of 100 Hz and pulse duration of 200 μs.

Participants will be asked about their perception of the stimuli every 5 min during the intervention. For both tDCS and PES sham procedures, the devices will be ramped up for 30 s and then decrease until no electric current is delivered. To ensure blinding, participants will receive information that they may or may not feel the stimulation. Moreover, they will not be able to see the equipment. At the end of each intervention protocol, potential adverse effects and quality of blinding will be assessed by a self-report questionnaire.

### Clinical and sociodemographic characterization of the sample

Sample will be characterized through socio-demographic (gender, age, education level, profession, marital status, and race) and clinical data (anxiety/depression symptoms and disability index related to pain). Socio-demographic data will be collected by self-report questionnaire designed specifically for this study. Clinical data will be collected using the following instruments:

Hospital anxiety and depression scale (HADS): HADS comprises two seven-items subscales. Subjects will rate each item using an ordinal scale varying from zero (non-existent symptom) to three (very severe symptom) (Pais-Ribeiro et al., 2007).Pain Disability Index (PDI): PDI is composed of seven items to assess how pain interfere in daily activities, including: family and domestic obligations, recreation, social activities, profession, sexual life, autonomy, and elementary activities indispensable to life. Subjects will rate each item using an ordinal score ranging from zero (no disability) to 10 (total disability) (Tait et al., 1990).

### Outcome measures

#### Primary outcome measure

Pain intensity will be measured by the VAS, in two positions: participant sited comfortably and then sited abducting the most painful hip. The VAS ranges from zero to 10, where zero represents no pain at all and 10 the worst imaginable pain. This evaluation will be performed pre- and post-intervention.

#### Secondary outcome measures

A. Power density of electroencephalographic frequencies

Relative power density will be measured pre- and post-intervention. An electroencephalograph (EEG Brainet 36, EMSA, Brazil) with 30 electrodes arranged according to the international system of electroencephalography 10/10 will be used in the following electrode locations: F7 T3 T5 Fp1 F3 C3 P3 O1 F8 T4 T6 Fp2 F4 C4 P4 O2 Fz Cz Pz Oz FT7 FT8 TP7 CP3 FC3 CPz FCz CP4 FC4 TP8. EEG data will be collected at a sampling rate of 600 Hz and referenced to Cz channel. Impedance will be maintained below 5 kΩ for all electrodes. The recording environment will be kept in subdued light and protected by a Faraday cage. Participants will be instructed to sit comfortably in a chair, keeping their eyes closed during EEG recording, which will occur in the two conditions described below.

a. Resting state: This condition will last 4 min, and the participant will be asked to not focus on any specific cognitive activity;b. Kinesthetic motor imagery (Kinesthetic–MI): Kinesthetic–MI will follow the resting state recorded, divided into two distinct stages. (1) *Kinesthetic–MI of a movement in the non-painful region of the body:* After 10 s of recording, participants will hear a standardized command requesting to mentally simulate closing and opening the contralateral hand to the most painful hip side. The command to each mental simulation will be repeated eight times, being 5 s of closing movements and 10 s of opening movements of the hand, totaling 120 s. (2) *Kinesthetic–MI of a movement in the painful region of the body:* The same protocol described above will be repeated, but this time the command will be to mentally simulate the abduction and adduction of the most painful hip. Electromyographic (EMG) data of the *gluteus medius* muscle on the most painful side and flexor muscles of the fingers contralateral to the hip will be also recorded to ensure absence of real movement. After each recording, the quality of the Kinesthetic–MI will be assessed by the kinesthetic and visual imagery questionnaire (KVIQ) (Malouin et al., 2007). EEG recording will take ~1 h.

Pre-processing of EEG data will be done using the MATLAB software version 2015 and EEGlab *toolbox* version 14. The signals will be filtered offline with a bandpass between 0.5 and 45 Hz. EEG data will be segmented into epochs of 1.71 s to allow an analysis of power densities at frequencies ranging from 1.2 to 30 Hz. EEG artifacts with minimum amplitude below −750 or maximum amplitude above 750 μV will be rejected using a semi-automated protocol. EEG data with more than 33% of rejected epochs will be excluded from further analyses. After the artifact rejection protocol, all EEG data will be adjusted to have the same number of epochs.

Power density will be calculated by fast Fourier transform in each epoch and electrodes, separately for each participant. The average power densities will be grouped in delta (1.2–3.5 Hz), theta (4–7 Hz), alpha (8–12 Hz), and beta (13–30 Hz) frequency bands. Regions of interest (ROI) chosen for analysis will be computed by averaging power densities for the following groups of electrodes: frontal (F7, F3, Fp1, Fz, Fp2, F4, F8), central (FC3, C3, FCz, Cz, C4, FC4), parietal (CP3, P3, CPz, Pz, CP4, P4) temporal (FT7, T3, TP7, T5, FT8, T4, TP8, T6), and occipital (O1, Oz, O2). After obtaining absolute power densities, the relative power density will be calculated dividing electrode's values in each one of the analyzed frequencies by their values in the total power spectrum.

B. TMS cortical mapping

Cortical mapping will be assessed pre- and post-intervention. After EEG recording, each participant will be asked to lie down comfortably in a supine position on an examination table, with head and neck resting on a support. The TMS cortical mapping will be performed using a single-pulse TMS apparatus (Bi-Stim; Magstim Co. Ltd, Dyfed, UK) delivered over M1 to cover the representation of both *gluteus maximus* muscles. A figure-of-eight coil will be positioned with the handle oriented backwards and aligned to the sagittal suture, inducing a postero-anterior flow of current. One cap marked with an 8 × 7 cm grid and oriented to the vertex will be placed on the participant's head and regularly checked to guarantee placement consistency. The vertex will be marked on the intersection of interaural and nasion to inion lines according to the 10/20 international EEG system.

The stimulus intensity for mapping will be set at 120% of Active Motor Threshold (AMT) for the *gluteus maximus* muscle. AMT will be the minimum intensity at which a TMS stimulus evokes a response of 200 μV while the *gluteus maximus* muscle is contracted under a comfortable bridge position in supine. Then, the AMT will be determined using the adaptive TMS motor threshold assessment tool (MTAT 2.0). The TMS pulse will be applied every 6 s, with a total of five stimuli at each site on the 8 × 7 cm grid.

Surface electrodes Ag/AgCl (3M, USA) will be used to record EMG activity at the *gluteus maximus* muscles, bilaterally. The two registering electrodes will be placed at 50% on the line between the second sacral vertebrae (S2) and the hip greater trochanter. The positioning of the electrode will be determined after palpation of the *gluteus maximus* muscle during a moderate voluntary contraction. The reference electrode will be placed over the hip greater trochanter or S2 (Fisher et al., 2013). The EMG signals will be amplified 3,000 times, filtered, bandpassed between 1 Hz and 2 kHz, with sampling rate maintained at 4 kHz using Signal v.06 software (Cambridge Electronic Design, UK). EMG data elicited by TMS will be monitored in real time to ensure the consistency of evoked responses (Signal, Cambridge Electronic Design, UK). Mapping of the *gluteus maximus* muscle will take ~40 min.

TMS map volume and center of gravity (CoG) of both *gluteus maximus* muscles will be used as dependent variables. These parameters will be calculated, respectively, by the sum of normalized MEP amplitudes at each site and by the formula:

$$\text{CoG}=\sum {\text{V}}_{\text{iX}}{\text{X}}_{\text{i}}/\sum {\text{V}}_{\text{i}};\sum {\text{V}}_{\text{iX}}{\text{Y}}_{\text{i}}/\sum {\text{z}}_{\text{i}}$$

Where, V_i_ = mean MEP amplitude at each site with the coordinates X_i_, Y_i_

C. Serum levels of BDNF and TNF

Serum levels of BDNF and TNF will be measured pre- and post-intervention. Approximately 5 mL of blood will be collected from each study participant and stored in test tubes with anticoagulant EDTA (0.03%). This procedure will last <5 min. The blood sample will be centrifuged at 2,500 rpm for 10 min and the plasma stored at a temperature of −40°C.

At a later time, serum levels of BDNF and TNF will be quantified using enzyme-linked immunosorbent assay kits (DuoSet, R&D Systems, Minneapolis, MN). A volume of 100 μL of monoclonal antibody-based capture will be added to a 96-well plate, which will be incubated for 12 h at room temperature (RT). The wells will be washed with wash buffer (PBS/Tween) and incubated with a blocking solution (300 μL) containing PBS and bovine serum albumin (BSA) for 1 h at RT. Samples and standards will be plated and incubated for 2 h at RT. After washings, the detection monoclonal antibody will be added to the plate and incubated for 2 h at RT. Then, a streptavidin-peroxidase solution will be added and incubated for 1 h at RT.

Finally, the substrate solution (H_2_O_2_ and TMB tetramethylbenzidine) will be added to the plate and a blue color will develop within a period of 20 min. The staining reaction will be stopped by adding H_2_SO_4_ 2N, and the reading will be made on a microplate reader at 450 nm. Levels of BDNF and TNF will be expressed in pg/mL and calculated from the reference values obtained with a standard curve built with known concentrations of recombinant BDNF and TNF. Concentrations of BDNF and TNF in plasma will be quantified using commercially available antibody pairs and recombinant cytokine standards (DuoSet, R&D System, Minneapolis, MN), using sandwich enzyme-linked immunosorbent assay (ELISA) according to the manufacturer's instructions.

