### Hypothesis

A single session of anodic tDCS associated with sensory PES provides greater analgesic effect compared with single use of the techniques;

The association of anodic tDCS and sensory PES causes greater decrease on serum levels of BDNF and TNF and greater increase on the muscle *gluteus maximus* cortical representation compared to the individual use of the techniques;

A session combining anodic tDCS and sensory PES leads to greater decrease of electroencephalographic low frequency (delta, theta, and alpha) power density compared to the individual use of the techniques in participants with SCD.

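### The only stated EEG rejection limit, ±750 µV, would not by itself remove ordinary eye or movement deflections, so delta power can be inflated and the 33% exclusion rule left idle

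*Protocol article*

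**What the plan says.** The EEG processing is described in the protocol article under Secondary outcome measures, part A. The steps, in the order given, are:

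- Filter: "The signals will be filtered offline with a bandpass between 0.5 and 45 Hz".
- Epochs: "EEG data will be segmented into epochs of 1.71 s to allow an analysis of power densities at frequencies ranging from 1.2 to 30 Hz".
- Rejection: "EEG artifacts with minimum amplitude below −750 or maximum amplitude above 750 μV will be rejected", by a procedure described as semi-automated.
- Recording-level rule: "EEG data with more than 33% of rejected epochs will be excluded from further analyses".

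Delta is defined as 1.2–3.5 Hz. The frontal region of interest has seven electrodes and includes Fp1, Fp2, F7 and F8. The analysed quantity is relative power, that is, power in a band divided by total power. All recordings are made with eyes closed. The Hypothesis section expects the combined treatment to produce a "greater decrease of electroencephalographic low frequency (delta, theta, and alpha) power density". No reason is given for the value 750, and no ocular correction step is named.

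**The concern.** An amplitude limit is there to remove epochs in which something other than brain activity dominates the signal. If background EEG is of the order of tens of µV, and eye and movement deflections are of the order of one to a few hundred µV (both assumptions), then a limit of 750 µV lies above both and separates nothing. The 0.5–45 Hz filter does not help, because slow deflections lie inside its pass band and overlap delta, one of the bands in which an effect is hypothesised. The electrodes nearest the eyes sit in the frontal region.

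The two quality rules also fit together poorly. A cut-off at 33% of epochs rejected is useful only if the epoch-level criterion rejects a material share of epochs. At stake are the precision of the delta results and, through the common denominator, the relative power of the other bands.

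**Working it through.** The ±750 µV limit is set, not derived, so there is no calculation of the plan's to reproduce. The neighbouring EEG figures are consistent:

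- Samples per epoch: 1.71 s × 600 Hz = 1026. Frequency resolution: 1/1.71 = 0.585 Hz. Two bins = 1.17 Hz, which matches the stated lower edge of 1.2 Hz.
- Epochs per recording: 240 s / 1.71 s ≈ 140 at rest, and 120 s / 1.71 s ≈ 70 in each imagery stage.
- Rejections needed to pass 33%: 0.33 × 140 = 46.2, so 47 epochs at rest; 0.33 × 70 = 23.1, so 24 epochs in an imagery stage.

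**Simulation.** From the document: 600 Hz, 1026-sample epochs, the 0.5–45 Hz filter, delta 1.2–3.5 Hz. Assumed, because the article gives no values: background of 1/f noise plus a 10 Hz peak at 10, 20 or 30 µV RMS; one Gaussian deflection (SD 80 ms) of 50 to 700 µV; and the share p of epochs that hold one.

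**Step 1: does the limit reject?** The 99th percentile of the peak in clean epochs was 41, 79 and 125 µV at 10, 20 and 30 µV RMS. The limit is therefore 750/125 = 6 to 750/41 ≈ 18 times that peak. Rejection at 20 µV RMS:

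| Limit | Clean | 50 µV | 100 µV | 200 µV | 400 µV | 700 µV |
|---|---|---|---|---|---|---|
| ±750 | 0% | 0% | 0% | 0% | 0% | 0% |
| ±100 | 0% | 1% | 47% | 100% | 100% | 100% |
| ±75 | 4% | 24% | 97% | 100% | 100% | 100% |

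At 10 and 30 µV RMS the ±750 limit also rejected 0% throughout. On amplitude alone the count is therefore 0, against the 47 or 24 needed for the 33% rule to act.

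**Step 2: effect on delta.** Let R be delta power in a contaminated epoch divided by that in a clean one. Mean delta power is multiplied by (1 − p) + pR, and the part of delta carried by contaminated epochs is pR / [(1 − p) + pR]. At 20 µV RMS, R = 7.5 for 100 µV and 27.1 for 200 µV:

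- p = 2%, 100 µV: 0.98 + 0.15 = 1.13-fold; contaminated epochs carry 0.15/1.13 = 13%.
- p = 10%, 100 µV: 0.90 + 0.75 = 1.65-fold; 0.75/1.65 = 45%.
- p = 10%, 200 µV: 0.90 + 2.71 = 3.61-fold; 2.71/3.61 = 75%. Relative delta goes from 0.18 to 0.44, so the share left for all other frequencies falls from 0.82 to 0.56.

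Range of the multiplier over the assumed background:

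| Case | 10 µV RMS | 20 µV RMS | 30 µV RMS |
|---|---|---|---|
| 2%, 100 µV | 1.52 | 1.13 | 1.06 |
| 10%, 100 µV | 3.61 | 1.65 | 1.29 |
| 10%, 200 µV | 11.4 | 3.61 | 2.16 |

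**Step 3: when would contaminated epochs carry more than half of delta?** When p exceeds 1/(1 + R). Over 10 to 30 µV RMS this is 12–37% of epochs at 50 µV, 4–20% at 100 µV, 1–7% at 200 µV and 0.2–2% at 400 µV.

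These are single-channel figures. Averaging over the seven frontal electrodes weakens the effect to the extent that a deflection does not reach all of them.

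**The case against.** The strongest reply is that the amplitude limit is not the whole procedure. The same sentence says that epochs "will be rejected using a semi-automated protocol", which implies a part that is not automatic. A condensed article may leave that part, such as visual inspection or component removal, to the full protocol. This stands: the statement that the 33% rule would not act holds for amplitude alone, and missing detail on the other part is not an error. It does not rescue the stated number, which does no work as a rejection criterion.

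Second, recordings are made with eyes closed, and EMG of a hip muscle and the finger flexors checks for real movement. Eyes-closed recording lowers the blink rate, so a 10% contaminated share may be too high. It does not stop slow eye movements or lid flutter, and the EMG does not cover the eyes, jaw or head.

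Third, a reader might infer that active tDCS biases the EEG comparison, because one electrode lies over the supra-orbital region and the Potential adverse effects section lists somnolence and skin sensations. The documents do not say that these persist into the later EEG or that they are absent under sham, which also starts with a current ramp. With similar artifact rates in all arms, the result is noise in the group-by-time comparison.

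Fourth, a tighter limit can cost data. At 30 µV RMS, ±100 µV rejects 14% of clean epochs and ±75 µV rejects 75%, which would itself trip the 33% rule. This stands and shapes the remedy.

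**Conclusion.** The point holds in a limited form. As an amplitude criterion, ±750 µV would not reject deflections of up to several hundred µV, and on amplitude alone it leaves the 33% rule idle. That result held at every background level and deflection size tried and does not depend on the contaminated share.

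The size of the consequence does depend on assumptions. At 20 µV RMS, delta power rises from about 1.13-fold (2% of epochs at 100 µV) to 3.6-fold (10% at 200 µV), mainly in the frontal region, with a matching loss of relative power elsewhere. A reader might conclude that delta will be dominated by contaminated epochs. The documents do not support that: they give neither artifact sizes nor rates, and in several of the cases above contaminated epochs carry less than half of delta power. A tenfold misprint is possible but cannot be shown from the text.

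The main effect is added noise in a secondary outcome. Bias between arms would arise only if artifact rates change differently by arm. The primary pain outcome, the sample size and alpha are not touched.

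**What to change.** Before any unblinded EEG analysis:

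1. Check the ±750 µV figure against the full protocol or the processing script, correct it if it is a misprint, and state what else the semi-automated step rejects.
2. Remove ocular components in EEGLAB, which the article already names.
3. Then apply a tighter amplitude limit, of the order of ±100 µV. Choose it from the pooled recordings, blind to arm and time point, so that few clean epochs are lost. The documents do not determine one value. A limit of ±100 µV without step 2 would have missed about half of the epochs with 100 µV deflections at 20 µV RMS.
4. Keep the 33% rule and apply it to the corrected limit.

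The cost is one offline processing step on recorded data, somewhat more rejected epochs and possibly some excluded recordings.

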### Potential adverse effects

The tDCS has relatively minimal adverse effects, which include: mild tingling; itching; burning and mild pain sensation under the surface of the electrodes; fatigue; and somnolence (Poreisz et al., 2007). The main adverse effects of PES are, skin irritation and local allergic reaction (Coutaux, 2017). Nonetheless, none of these adverse events are considered to be serious. These potential adverse effects may be avoided by appropriate training in the handling of the technique. The use of TMS to evaluate the motor cortical representation of the *gluteus maximus* muscle also has some potential risks such as seizures, syncope, and headache (Rossi et al., 2009), but all are rare and will be duly clarified to participants during recruitment and signature of informed consent. The Clinical Electrophysiology Laboratory team has trained physical therapists and physicians accessible to assist in case any harm occurs to a participant. Any adverse effect that may occur during the study, even those not directly related to the study assessments and interventions, will be reported to the Institutional Review Board.

